### Statistical Methods

The power calculation was based on the analyses of the primary outcomes, that is, aerobic capacity (VO_2_peak) and experimental stress reactivity (saliva cortisol). On the basis of the results of Bacon et al [122], the sample size was determined a priori via power analysis (G*Power V5), yielding a minimum sample size of 67 for a medium-to-large effect size of *f(V)*=0.35. An alpha error set to .05 and statistical power of 0.80 were assumed for a multivariate analysis of variance (MANOVA) with 2 repeated measurements, 2 groups, and interaction effects. Descriptive statistics will be used for all outcome measures at each time point to give an overview of all results. First, MANOVA will be performed with the main primary outcomes as dependent variables, that is, aerobic capacity (VO_2_peak) and experimental stress reactivity (saliva cortisol) to maximize the power of the analyses and to be able to investigate the main and interaction effects of time (baseline [T0, T1] vs post [T2, T3]) and group (IG vs CG). Groups should be equal at preintervention (T0 and T1). A time effect should be observed for the IG. Furthermore, we expect a significant time×group interaction as the IG should react differently over time, with a higher increase in aerobic capacity (VO_2_peak). Significant effects of the MANOVA will be followed up by posthoc analyses of variance. As a secondary aim of our study, we aim to identify variables (eg, emotion regulation and biological metrics) that mediate the relationship between physical exercise and resilience outcomes. To that end, we plan to calculate multiple regression analyses that include potential mediators. Principal component analyses regarding potential mediating variables will precede the mediator analyses to avoid redundancy in our regression models. This will be statistically detailed with posthoc tests and corrections for multiple comparisons (Bonferroni-Holm correction [123]). Missing data will be omitted from the data set.

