
Here, we selected an exercise intervention period of 8 weeks using a combination of interval-type training and continuous endurance exercise to efficiently enhance aerobic capacity in a short period. Interval training improves VO_2_peak more strongly in comparison with continuous exercise training [8]. Moreover, psychological benefits in attention, complex attention, and executive function were shown in high-intensity interval training compared with those in low-intensity training [133-135]. However, to counteract overtraining and risk of injury and to promote adherence, we complement interval-type training with endurance exercise sessions. A number of high-intensity interval training and moderate-intensity intervention studies with physically inactive participants decided for a comparable exercise intervention time leading to significant increases in VO_2_peak of 3%-19% [9-11]. Although a longer intervention period generally leads to higher increases in maximal oxygen uptake [122], it has been reported that enjoyment of interval training decreases with time [10]. Therefore, we considered a study design that used mixed model exercise sessions with a short intervention time of 8 weeks as efficient to enhance aerobic capacity in physically inactive adults and as suitable to analyze the impact on resilience.

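### The 67 participants give 80% power for one outcome measured twice; the planned two-outcome MANOVA has about 71% at the same stated effect, and no cortisol effect size is given

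*Protocol article*

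**What the plan says.** All of the power inputs stand in the Statistical Methods section. It opens with the claim that "The power calculation was based on the analyses of the primary outcomes", and names VO2peak and saliva cortisol as those outcomes. The effect size rests on one reference, [122], "yielding a minimum sample size of 67 for a medium-to-large effect size of *f(V)*=0.35". The error rates and design behind the number are given as follows: "An alpha error set to .05 and statistical power of 0.80 were assumed for a multivariate analysis of variance (MANOVA) with 2 repeated measurements", with two groups and an interaction.

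The same section then sets out the primary analysis: "MANOVA will be performed with the main primary outcomes as dependent variables, that is, aerobic capacity (VO_2_peak) and experimental stress reactivity (saliva cortisol"), over time and group. It gives maximising power as a reason for choosing this model, and says that missing data will be omitted.

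Elsewhere, the trial registration data set gives a target of 70, Randomization gives equal allocation, and Results reports 11.4% dropout so far. Strengths and Limitations cites the same reference for the statement that "a longer intervention period generally leads to higher increases in maximal oxygen uptake [122"]. That section also says that the stress measures at T0 and T2 are not directly comparable, and that the design therefore does not allow within-subject analyses.

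**The concern.** The stated design inputs are the number of repeated measurements, the number of groups and the interaction. The number of dependent variables is not among them. A MANOVA on two outcomes spends an extra degree of freedom, so for the same f(V) it needs more participants than a single-outcome test. If 67 came from the single-outcome case, the stated 80% belongs to a different test from the one planned.

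Cortisol is a primary endpoint and the main laboratory measure of resilience. If the power statement is taken at face value, a null cortisol result could be read against an 80% power that was never worked out for it.

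**Working it through.** **Inputs.** From Statistical Methods: f(V)=0.35, so f²=0.1225; alpha 0.05; power 0.80; 2 groups; 2 measurements; stated N=67. From the registration data set: target 70. From Results: dropout 11.4%. Allocation is 1:1.

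**Formula.** The noncentrality is λ = N·f². For p outcomes, each measured before and after in two groups, the interaction test is a two-group comparison of p change scores, with F on p and N−1−p degrees of freedom. Power is the probability that a noncentral F with that λ exceeds the 5% critical value.

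**Step 1: reproduce the stated 67 (p=1).**
- N=66: λ=8.085, F(1,64), power 0.7997.
- N=67: λ=67×0.1225=8.2075, F(1,65), critical value 3.989, power 0.8058.

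So 67 is exactly the smallest N for one outcome measured twice. Other readings do not give 67: univariate repeated-measures ANOVA gives 11 to 59 (correlations 0 to 0.75), 0.35 read as f² gives 25 or 31, and three or four dependent variables give 94 or 103.

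**Step 2: the planned two-outcome test, with 0.35 as its joint effect (p=2).**

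| N | λ | df | Power |
|---|---|---|---|
| 62 | 7.595 | 2, 59 | 0.670 |
| 67 | 8.2075 | 2, 64 | 0.708 |
| 70 | 8.575 | 2, 67 | 0.729 |
| 82 | 10.045 | 2, 79 | 0.801 |

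The minimum for 0.80 is 82. Conversely, 80% at N=67 would need a joint f(V) of about 0.39.

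**Step 3: 0.35 read as the VO2peak effect alone.** With equal groups d=2f=0.70. For uncorrelated changes the joint f² is 0.1225 + d²/4, where d is the cortisol effect (assumed values, since the protocol gives none).
- d=0: f²=0.1225; 0.708 at 67, 0.729 at 70.
- d=0.3: f²=0.1225+0.0225=0.145; 0.783 at 67, 0.803 at 70.
- d=0.35: f²=0.1531; 0.807 at 67.
- d=0.5: f²=0.185; 0.878 at 67.

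If both outcomes had f=0.35, power at 67 would be 0.95, 0.83 and 0.76 at change-score correlations of 0, 0.5 and 0.8 (assumed).

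**Step 4: cortisol on its own at N=67** (1-df between-group contrast, assumed d): 0.23 at d=0.3, 0.52 at d=0.5, 0.81 at d=0.7. The detectable difference at 80% is therefore about d=0.7.

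**Step 5: attrition.** 70×(1−0.114)=62.02, so about 62 analysed if missing data are omitted. Power at 62 is 0.774 for one outcome and 0.670 for two.

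**The case against.** The strongest reply is that 71% is not the power of the planned test under every reading. If 0.35 is the VO2peak effect, a second outcome cannot reduce the joint effect. The 0.708 is then the floor at N=67, reached for instance when cortisol adds nothing and is uncorrelated. A modest cortisol effect of d=0.3 brings the MANOVA to 0.803 at the target of 70, and d=0.35 or more matches or beats the single-outcome 0.806 at 67. Even with no cortisol effect, a correlation of 0.5 gives 0.833. This stands. A reader might infer that the true power is simply 71%, or that the MANOVA is shown to lose power. The document supports neither, because it states no cortisol effect and no correlation. What follows is that 80% is not demonstrated for the planned test.

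A second reply concerns the source. A reader might state as fact that the effect size comes from oxygen-uptake data. Statistical Methods does not say which outcome [122] informed. Its use in Strengths and Limitations shows only that it is cited for oxygen uptake, so the origin is an inference. That no cortisol effect size is stated is not an inference.

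A third reply is that the target of 70 exceeds 67. It does, but at a joint 0.35 it gives 0.729, and it does not cover the dropout already reported.

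**Conclusion.** The point holds. The stated 67 for 80% power belongs to the 1-df interaction of one outcome measured twice. It does not belong to the two-outcome MANOVA that the same section plans. At the stated f(V)=0.35, taken as the joint effect, the planned test falls short of 80% by about 9 points at 67 (0.708) and 7 points at 70 (0.729).

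The size of the shortfall rests on that reading of f(V). If 0.35 describes VO2peak alone, the shortfall could be as large as this or could vanish, depending on unstated cortisol inputs. With uncorrelated outcomes, a cortisol effect of about d=0.3 is enough to reach 80% at 70 analysed. The mismatch between the calculation and the planned test does not depend on the reading.

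The claim that the calculation covers cortisol, and the claim that the MANOVA maximises power, are unsupported; neither is disproved.

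**What to change.** Revise the wording of Statistical Methods:

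1. Say that 67 analysed participants give 80% power for the VO2peak interaction alone (f(V)=0.35, d=0.70 on change).
2. Say that the two-outcome MANOVA has about 71% at 67 and 73% at 70 if 0.35 is the joint effect. If a cortisol effect and a correlation are assumed instead, state and justify them.
3. Give the figures at the number expected to be analysed: about 62 of 70 at 11.4% dropout, with 77% for one outcome and 67% for two.
4. State separately the detectable cortisol difference, about d=0.7 at 80% with 67 analysed. Define it as a between-group contrast at T2, because the protocol itself says that the T0 and T2 stress measures are not directly comparable. A pre-post cortisol change would conflict with that limitation.
5. Remove the statement that the MANOVA maximises power, or justify it with the assumed cortisol effect and correlation.

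The cost is protocol text and a less favourable power statement. No extra participants are needed. Results says that recruitment is paused short of the target, so the text can be corrected before data collection is complete.

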### Objectives

In this study, we implement an 8-week randomized controlled trial of a web-based, individualized physical exercise training intervention to evaluate the link between aerobic capacity and resilience in healthy untrained adults. Therefore, baseline values of performance diagnostics to determine the innate aerobic capacity (VO_2_peak) as well as emotion regulation abilities, stress reactivity, and stress recovery (saliva cortisol) as potential resilience mechanisms are estimated. We hypothesize that (1) participants with a high innate aerobic capacity will show a higher resilience to stress compared with participants with low aerobic capacity. This will be followed by 8 weeks of individualized web-based physical exercise training combining continuous and interval-type running exercises with the aim of progressively increasing aerobic capacity. After completion of the exercise intervention, performance diagnostics will be repeated to estimate the acquired aerobic capacity, as well as to assess the psychological parameter. In addition, secondary outcomes of molecular factors, including hair cortisol levels, endocannabinoids, catecholamines, cytokines, and cell-free DNA, and results of several questionnaires will be determined throughout the study. We hypothesize that (2) the exercise intervention will improve the aerobic capacity of the intervention group, which (3) will be accompanied by improvements in resilience factors. This will offer the possibility to exploratively study the underlying molecular mechanism (stress hormone release and immune reactions) in the promotion of resilience by regular physical activity.

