### Randomization

The included participants will be randomly assigned with a 50%-50% allocation to the IG or CG. Randomization will be performed using the EXCEPT NUMBER command in Microsoft Excel. In addition, randomization will be stratified by gender with an expected ratio of 50%-50% and BMI with an expected ratio of 33% overweight (BMI ≥25) and 67% normal weight (BMI <25) to recruit CG and IG participants with homogeneous baseline characteristics.

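### The time×group interaction is not fixed as the sole deciding effect, and time effects that do not compare training with control are tested and followed up beside it

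*Protocol article*

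**What the plan says.** All references are to the protocol article.

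- **Sample size (Statistical Methods).** One alpha of .05 and power of 0.80 are set for a MANOVA "with 2 repeated measurements, 2 groups, and interaction effects", "yielding a minimum sample size of 67 for a medium-to-large effect size of *f(V)*=0.35".
- **Primary analysis (same section).** A MANOVA on VO2peak and saliva cortisol is meant to "be able to investigate the main and interaction effects of time" and group.
- **Expectations (same section).** The groups should be equal before the intervention. "A time effect should be observed for the IG". A significant time×group interaction is then also expected, with a larger VO2peak gain in the IG.
- **Follow-up rule (same section).** "Significant effects of the MANOVA will be followed up by posthoc analyses of variance". The rule does not distinguish between effects.
- **Multiplicity (same section).** The Bonferroni-Holm sentence comes after the mediator regressions and is not tied to the MANOVA effects.
- **Hypothesis 2 (Objectives).** "the exercise intervention will improve the aerobic capacity of the intervention group". No comparator is named. The first registered primary outcome (Textbox 1) also names none.
- **Stressors (Psychological Stress Tests; Strengths and Limitations).** T0 uses the cold pressor test and T2 uses ScanSTRESS. The limitations text says that measures from the two tests cannot be compared directly and that the design rules out within-subject analysis.

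**The concern.** Only the interaction, which is the between-arm difference in change, estimates the randomised effect. The other effects answer different questions:

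- **Time main effect and IG-only time effect.** Both contain whatever moves the two arms together, such as familiarity with the treadmill test, season or general drift.
- **Cortisol over time.** The comparison also contains the switch of stressor. A cortisol shift from that switch alone could make the time MANOVA significant and set off follow-up ANOVAs, including one for VO2peak.
- **Group main effect.** It averages pre and post values, so it carries chance baseline imbalance and dilutes any training effect. It is a weak route to a training claim.

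What is at stake is the claim for hypothesis 2. With a gain shared by both arms, the IG time effect can be significant while the interaction is null. The text does not say that the interaction must then prevail.

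**Working it through.** **Inputs from the document.** Alpha .05; power 0.80; f(V)=0.35; 2 groups; 2 measurements; 1:1 allocation (Randomization); target of 70 participants (Abstract), hence 35 per arm.

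**Assumptions not in the document.** Test-retest correlation 0.7 (0.85 also tried); correlation between the two outcomes 0 (0.3 also tried); size of any shared gain, as stated below.

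**Step 1: reproduce the stated 67.** For a 1-df interaction test with 2 groups and 2 measurements, power = P(F' > F crit), where F' is noncentral F with df1 = 1, df2 = N−2 and λ = f(V)²·N.

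- N = 66: λ = 0.1225 × 66 = 8.085; power 0.7997.
- N = 67: λ = 0.1225 × 67 = 8.2075; power 0.8057.

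The smallest N reaching 0.80 is 67, as stated. The sample size is therefore that of a single interaction test at .05.

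**Step 2: false-positive rates with no change in either arm.** Each test is run at .05 (Hotelling or F tests, 40,000 simulated trials, 35 per arm). A trial counts as positive if any listed effect is significant.

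| Effects counted | One outcome | Two outcomes |
|---|---|---|
| Interaction only | 0.051 | 0.049 |
| Interaction or IG-only time | 0.086 | 0.083 |
| Interaction or time main effect | 0.099 | 0.096 |
| Interaction, time or IG-only time | 0.117 | 0.117 |
| Interaction, time or group | 0.143 | 0.141 |
| All four | 0.161 | 0.160 |

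Three independent tests would give 1 − 0.95³ = 0.1426, in line with the fifth row. The alternative correlations did not change these rates.

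**Step 3: shared gain, no training effect.** For the IG-only paired test with n = 35, the noncentrality is δ√35, where δ is the shared gain in SDs of the change score. The two-sided critical t is 2.032 on 34 df.

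- δ = 0.2: noncentrality 1.18; rejects 21%.
- δ = 0.3: noncentrality 1.77; rejects 41%.
- δ = 0.5: noncentrality 2.96; rejects 82%.

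The simulation shows the same pattern. With a common shift of 0.1, 0.2 or 0.3 SD of the outcome itself, the interaction or the IG-only time effect is significant in 0.146, 0.345 or 0.629 of trials with one outcome. With two outcomes, both shifted, the figures are 0.165, 0.459 and 0.813. The interaction alone stays at 0.05 throughout.

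**Step 4: set the cortisol passages side by side.** Statistical Methods puts cortisol into a MANOVA with a time effect from T0 to T2. Strengths and Limitations says the two stress tests are not directly comparable and excludes within-subject analysis. A time effect on cortisol is such an analysis, so the two sections conflict.

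**The case against.** A reader might infer that the plan gives several alternative routes to a training claim and so roughly doubles the stated .05. The document does not support that.

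- **No either/or rule is written.** The expectations are listed in sequence and read naturally as cumulative. If both the IG time effect and the interaction were required, the false-positive rate could not exceed the interaction's .05.
- **The text leans on the interaction.** The 67 reproduces as its 1-df test, and it is the only effect whose significance is predicted.
- **A single multiple is arbitrary.** The figure runs from about 1.7 to about 3.2 times .05 depending on which effects are counted. Whether error should be controlled across the main effects and interaction of a factorial model is partly convention.
- **Hypothesis 2 can be read causally.** Inside a randomised trial, improvement through the intervention can imply a comparison with control.
- **The article is condensed.** Allocation of alpha across model terms is often left to an analysis plan, and the Holm sentence mentions post hoc tests, so it might reach the follow-up ANOVAs.

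The first three points stand, and they limit the finding to a criterion that is not fixed. The other two do not remove it. The article states its follow-up rule, and that rule covers time effects. Holm adjustment, even if it applied, would not turn a time effect into a test of training against control. The cortisol conflict lies within the article itself. Within the interaction, a MANOVA followed by one ANOVA per outcome at .05 is a valid closed test for two outcomes and is not criticised here.

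**Conclusion.** The point holds in limited form. The interaction is the basis of the sample size and the stated expectation, but it is not declared the sole deciding effect. Time, group and IG-only time effects stand beside it without a defined role.

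The inflation is conditional on any one effect being accepted as support: about 0.08-0.12 for the interaction plus time-related effects and about 0.16 for all four, with no change in either arm.

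The weightier part is that the rate for time effects has no fixed bound once both arms change. The 21%, 41% and 82% figures rest on assumed shared gains, which the document does not give, and on the IG-only test being taken as decisive, which the document does not say. For cortisol, the conflict with Strengths and Limitations needs no assumption.

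**What to change.** In Statistical Methods:

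1. State that the between-arm comparison (time×group interaction) is the only confirmatory effect, tested by the MANOVA at .05 and, if significant, for VO2peak and for cortisol separately at .05.
2. State that the time, group and IG-only time effects are descriptive and that no follow-up test on them supports a claim.
3. Reconcile the cortisol time comparison with Strengths and Limitations, for example by comparing the arms on the T2 cortisol response with the T0 response as covariate.

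In Objectives, and where the hypothesis is repeated in the Discussion, reword hypothesis 2 so that VO2peak improves more in the IG than in the CG.

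The cost is a few sentences and no new data. The article reports 31 completers and recruitment still open, so this can be settled before the final analysis. The small downside is that within-arm and main effects can no longer be reported as confirmatory. The minimum of 67 is unchanged on the document's own calculation. As a separate matter, that calculation is for a 1-df test. At the same f(V), a two-outcome interaction test (df1 = 2, df2 = N−3) has power 0.71 at N = 67 and needs N = 82. If that matters to the sponsor, a fixed order of VO2peak then cortisol, each tested at .05, keeps the 1-df basis.

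### Randomisation is stratified by gender and BMI category, but the stated primary MANOVA names only time and group; precision is lost if these factors predict change, and adding them costs almost nothing

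*Protocol article*

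**What the plan says.** Protocol article, Randomization: allocation is 1:1, and "randomization will be stratified by gender with an expected ratio of 50%-50% and BMI with an expected ratio of 33% overweight" (BMI 25 or above) against 67% normal weight. The stated aim is arms that are alike at baseline. The procedure is a random-number command in a spreadsheet; no blocks are described.

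Protocol article, Statistical Methods: the dependent variables of the primary MANOVA are VO2peak and saliva cortisol. The model is to "investigate the main and interaction effects of time (baseline [T0, T1] vs post [T2, T3]) and group (IG vs CG"), and significant effects are followed by ANOVAs. The effect of interest is the interaction: "we expect a significant time×group interaction as the IG should react differently over time". Gender and BMI do not appear. The sample size rests on a MANOVA "with 2 repeated measurements, 2 groups, and interaction effects", "yielding a minimum sample size of 67 for a medium-to-large effect size of *f(V)*=0.35", with alpha .05 and power 0.80. Missing data are omitted.

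Protocol article, Strengths and Limitations: the stress-test readings at T0 and T2 come from different paradigms. The authors say that these readings cannot be compared directly and that the design rules out analyses within participants.

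**The concern.** When allocation is stratified on factors that predict the analysed quantity, a model that omits them still counts their variance as error. The standard error is then larger than it needs to be and power is forgone. Where allocation is also balanced within strata, the unadjusted test becomes conservative. The section says the MANOVA was chosen for its power, so leaving out factors already built into the design works against that aim.

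What is at stake is the precision of the time×group result, in a trial whose target of 70 leaves little room for dropout. Validity is not at stake: the omission does not bias the estimated group effect.

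**Working it through.** **Inputs from the protocol.** f(V)=0.35, alpha 0.05, power 0.80, minimum N 67, 2 groups, 2 measurements (Statistical Methods). Target 70 (trial registration data set). Dropout 11.4%, which is 4/(31+4) (Results). Gender 50/50, BMI 33/67 (Randomization).

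**Input assumed.** R², the share of the variance of the *change* explained by gender and BMI category. The documents give none; a range of 0 to 0.20 is shown.

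**Step 1: reproduce the plan's figure.** For the 2×2 interaction, use the noncentral F with df1 = 1, df2 = N − 2 and λ = f(V)²·N. At N = 67, λ = 0.1225 × 67 = 8.21 and power is 0.806. N = 67 is the smallest N that reaches 0.80, so the stated figure reproduces exactly. (Counting both outcomes, with df1 = 2 and df2 = N − 3, gives 82 and does not match, so the first form is used below.)

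**Step 2: add gender and BMI category.** Now λ = f(V)²·N/(1 − R²) and df2 = N − 4. The ratio of unadjusted to adjusted standard error is 1/√(1 − R²).

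| Assumed R² of change | SE ratio | Power, N=67 | N for 0.80 power |
|---|---|---|---|
| 0 | 1.00 | 0.805 | 67 |
| 0.02 | 1.01 | 0.813 | 65 |
| 0.05 | 1.03 | 0.825 | 63 |
| 0.10 | 1.05 | 0.845 | 60 |
| 0.20 | 1.12 | 0.884 | 54 |

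The unadjusted comparator is 0.806 at N = 67.

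**Step 3: allow for dropout.** 70 × (1 − 0.114) ≈ 62 completers. Unadjusted power is 0.774. Adjusted power is 0.773 at R² = 0 and 0.815 at R² = 0.10.

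**Step 4: what cancels and what does not.** This was simulated with N = 68, allocation balanced within the four strata, a true effect of 0.70 residual SD of change, and 5,000 runs per scenario.

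- Gender explains 40% of post-test variance but none of the change. For time×group, power is 0.810 unadjusted and 0.809 adjusted, with mean SE 0.242 in both. The level difference cancels.
- Gender explains about 10% of the variance of change. Power is 0.791 unadjusted and 0.824 adjusted, mean SE 0.255 against 0.241, and unadjusted type I error 0.034. (Here the effect is fixed against the residual SD; in Step 2, f(V) is fixed against the total SD, so the levels differ slightly.)
- Same 40% level effect, but the arms are compared on post-test values only. Power is 0.41 unadjusted and 0.64 adjusted, mean SE 0.384 against 0.296, and unadjusted type I error 0.009.

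The third scenario bears on cortisol. Cancellation needs a stratum effect that is the same at both times. With a cold-pressor task at T0 and a cognitive-social task at T2 there is no ground to assume this, and the article's own limitation points towards a comparison at T2. The 40% is an assumption chosen to show the mechanism.

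**Step 5: does conservatism depend on balance?** With simple randomisation inside strata at N = 68 and R² of 0.10, 0.20 and 0.30, unadjusted type I error was 0.048, 0.054 and 0.050. Adjustment still raised power, from 0.804 to 0.831 at R² = 0.10.

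**The case against.** Several points against the concern have force.

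- **The repeated-measures structure already does much of the work.** The obvious gender and BMI differences in VO2peak are differences in level, and time×group removes them. This stands. A reader might infer that known variance is being left in the error term; the documents do not show that either factor predicts change, so nothing is known here.
- **The plan's power is not undercut.** A reader might infer that part of the planned 0.80 is wasted or that N = 67 is wrong. Neither follows. The standardised effect fits the unadjusted model and 67 reproduces from it, so what is forgone is possible power on top of that.
- **Conservatism is not established.** A reader might infer a type I error clearly below 0.05. That requires balanced allocation within strata. The Randomization section describes no blocks, and Results shows 17 and 14 completers plus 2 withdrawals per arm, which does not settle the matter.
- **The fix may miss part of the mechanism.** Only the intervention group trains, so a gender difference in training gain is largely a three-way effect. By-time terms common to both arms capture only part of it. With the gender difference confined to that arm at nominal R² = 0.10, power moved only from 0.820 to 0.831.
- **The source is a condensed article.** Covariates may be listed in an analysis plan that is not shown. This limits the point to a recommendation. It does not remove it, because the article does state the factors of the primary model and the stratifiers are not among them.

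**Conclusion.** The point holds as a modest, conditional improvement. The trial stratifies on two factors that its stated primary model does not name. For the time×group test the gain from naming them is about 1 to 4 power points at an assumed R² of 0.02 to 0.10, and nil if the factors do not predict change. The practical case is better at about 62 completers, where unadjusted power is 0.774 and adjustment at R² = 0.10 would bring it back above 0.80.

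The case is strongest for cortisol, where stratum effects need not cancel across two different stressors, and in particular for any comparison made at T2 alone. The size there depends on how strongly gender and BMI relate to the cortisol response, which the documents do not quantify.

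The conclusion rests on the assumed R² values and on reading the model as the article states it.

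**What to change.** In Statistical Methods, add gender and BMI category as between-subject terms, together with their by-time terms, to the primary MANOVA and the follow-up ANOVAs, and test time×group within that model. The by-time terms matter: they are what takes stratum-related variance out of the change. Include both factors as covariates in any cortisol comparison made at T2 only. If the authors prefer to leave them out, the section should say why.

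The cost is one sentence, 2 degrees of freedom and no new data. If the strata explain nothing, about 0.001 of power is lost at N = 67 (0.806 to 0.805). Recruitment was paused and incomplete when the article was written, so the terms could still be specified before the final analysis.

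### The stated 0.80 power at N=67 is that of a one-outcome interaction test; the planned two-outcome MANOVA has about 0.71, and gating on it cannot raise power for the VO2peak hypothesis

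*Protocol article*

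**What the plan says.** All of the following is in the Protocol article.

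- **Sample size (Statistical Methods).** The calculation is described as "yielding a minimum sample size of 67 for a medium-to-large effect size of"; the value entered is f(V)=0.35. Error rate and target power are set as follows: "An alpha error set to .05 and statistical power of 0.80 were assumed for a multivariate analysis of variance (MANOVA". The design behind the calculation is described as one "with 2 repeated measurements, 2 groups, and interaction effects". The number of dependent variables is not among the stated inputs.
- **First step (Statistical Methods).** "First, MANOVA will be performed with the main primary outcomes as dependent variables", namely VO2peak and saliva cortisol. The reason given is "to maximize the power of the analyses and to be able to investigate the main and interaction effects of time"; the same is said for the group factor.
- **Second step (Statistical Methods).** "Significant effects of the MANOVA will be followed up by posthoc analyses of variance".
- **Hypotheses (Objectives).** Hypothesis 2 is that "the exercise intervention will improve the aerobic capacity of the intervention group". Hypothesis 3 is that improvement in resilience factors accompanies this. No effect size for cortisol and no correlation between the two outcomes is given.
- **Target.** The trial registration data set gives a target sample size of 70.

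**The concern.** The power figure and the planned test are both called a MANOVA, but they may not be the same test. With two measurements of one outcome in two groups, the multivariate time×group test has one numerator degree of freedom. With two outcomes analyzed together, it has two. If 0.80 belongs to the first and the trial opens with the second, the stated power is not that of the step on which everything else depends.

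The rationale is a second issue. A VO2peak conclusion requires a significant MANOVA and then a significant VO2peak ANOVA. Adding a condition cannot make that conclusion more likely. A real VO2peak gain could therefore go undeclared because a weakly responding cortisol measure diluted the joint test, while the reader has been told that the joint test maximizes power.

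This risk is not remote. The effect size is attributed to a source that Strengths and Limitations cites for gains in maximal oxygen uptake. Statistical Methods spells out an expected direction of the interaction only for VO2peak.

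**Working it through.** **Inputs from the article.** Alpha .05, f(V)=0.35 so f²=0.1225, two groups allocated 1:1, two measurements, N=67 (target 70).

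**Assumed, not in the article.** The cortisol effect and the correlation between the two changes. Both are varied below. Changes are treated as bivariate normal.

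**Step 1: reproduce the plan's figure.** Power is the probability that a noncentral F with λ = N·f² exceeds its critical value. For one outcome, df = 1, N−2.

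- N=67: λ = 67 × 0.1225 = 8.21, critical F(1,65) = 3.99, power **0.806**.
- N=66: λ = 8.09, power 0.7997.

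The smallest N reaching 0.80 is 67, exactly as printed. With λ = (N−2)·f² the answer is 68.

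**Step 2: the test that is planned.** For two outcomes, df = 2, N−3, with the same f(V).

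- N=67: critical F(2,64) = 3.14, power **0.708**.
- N=70: λ = 8.58, power **0.729**.
- N=81: power 0.796. N=82: power 0.801. The minimum is therefore 82.

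**Step 3: the gated claim.** The event that MANOVA and VO2peak ANOVA are both significant is contained in the event that the VO2peak ANOVA is significant. At the same alpha its probability cannot be larger, whatever cortisol does. The same holds for claiming both outcomes.

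**Step 4: size.** Simulation at N=67 with VO2peak f=0.35: Hotelling T² on the two change scores at .05, then the VO2peak ANOVA at .05. Cortisol is coded so that its effect has the same sign as that of VO2peak. If cortisol is coded as falling, the signs of the correlations reverse.

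| Cortisol f | Correlation of changes | VO2peak ANOVA alone | MANOVA, then VO2peak ANOVA |
|---|---|---|---|
| 0 | 0 | 0.81 | 0.70 |
| 0 | ±0.3 | 0.81 | 0.72 |
| 0 | ±0.5 | 0.81 | 0.76 |
| 0.2 | +0.5 | 0.81 | 0.70 |
| 0.2 | 0 | 0.81 | 0.76 |
| 0.2 | −0.5 | 0.81 | 0.80 |
| 0.35 | +0.5 | 0.81 | 0.76 |
| 0.35 | 0 | 0.81 | 0.80 |
| 0.35 | −0.5 | 0.81 | 0.81 |

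At N=70 with cortisol null and correlation 0, the figures are 0.82 alone and 0.72 gated. About 84 participants would be needed for 0.80 under the two-step rule in that scenario.

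**Step 5: an alternative order.** Suppose VO2peak is tested first at .05 and cortisol only if VO2peak is significant. The VO2peak test keeps 0.806. With f=0.35 on both and correlation 0, the cortisol claim has 0.65, against 0.80 under the present gate. Power to claim both outcomes is 0.65 under either rule.

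**The case against.** The defense of the present rule is substantial.

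- **It is a valid procedure.** With exactly two outcomes, a MANOVA at .05 followed by each ANOVA at .05 is a closed test that controls the family-wise error. It also compares well with Holm. For the VO2peak claim at correlation 0, gate versus Holm is 0.698 versus 0.719 with cortisol null, 0.758 versus 0.739 with cortisol f=0.2, and 0.798 versus 0.779 with f=0.35.
- **The 0.81 comparator is generous.** It is an unadjusted .05 test of one of two primary outcomes. Splitting alpha to .025 gives 0.715, so much of the apparent loss is the usual price of two primaries. Only a fixed order avoids it for VO2peak.
- **The rationale may refer to the pair.** The power remark is made of the analyses in general. With f=0.35 on both and correlation 0, the MANOVA itself has 0.95 power, and the rule supports at least one outcome in 0.946 of trials against 0.918 with Holm.
- **Cortisol is hypothesized to respond.** The 0.70 case supposes that hypothesis 3 fails.

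All of this stands. It shows that the gate is defensible and that its rationale can hold for the omnibus test. It does not make 0.80 the power of the two-outcome MANOVA at f(V)=0.35, and it does not make the rationale true for hypothesis 2.

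A reader might also infer that the gate causes the 0.65 power for claiming both outcomes. It does not: at correlation 0 that figure is the same with or without the gate.

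**Conclusion.** The point holds as a misstatement of power and of rationale. The printed 67 and 0.80 describe a 1-df test of one outcome (0.806). The two-outcome MANOVA that opens the analysis has 0.71 at the same f(V) and N=67, and 0.73 at 70. These figures need only the article's own inputs.

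That the gate cannot add power for hypothesis 2 is a matter of logic. How much it takes away depends on assumptions. The VO2peak claim falls from 0.81 to about 0.70 only if cortisol does not respond and the changes are uncorrelated. With cortisol null and correlations up to ±0.5, the range is 0.70 to 0.76.

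A reader might infer that 0.80 fits no claim that the two-step rule can produce. That goes too far. With f=0.35 on both outcomes and correlation 0, the gated VO2peak and cortisol claims each have about 0.80. Smaller cortisol effects come close when the correlation is favorable.

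One caution applies to every cortisol figure here. The simulation treats cortisol as an ordinary change score, although Strengths and Limitations says that measures from the two stress tests are not directly comparable.

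**What to change.** In Statistical Methods:

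1. State that 0.80 (0.806 at N=67, f=0.35) is the power of a time×group test of a single outcome.
2. Give the power of the two-outcome MANOVA at the same f(V): about 0.71 at N=67 and 0.73 at N=70.
3. Give the power of the gated VO2peak claim over a stated range of cortisol effects and correlations, for example those tabulated above.
4. Delete the power-maximizing rationale, or limit it to the omnibus test.

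These are wording changes. They need no extra participants or measurements.

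A fixed order, VO2peak at .05 and then cortisol at .05 only if VO2peak is significant, is an option for the sponsor, not a necessary correction. It keeps 0.806 for VO2peak and controls the family-wise error. Its cost must be named: the cortisol claim falls from about 0.80 to 0.65 if both effects are f=0.35 and uncorrelated. It should not be called cost-free on the ground that hypothesis 3 depends on hypothesis 2, because Benefits of the Study states hypothesis 3 without making it conditional on a VO2peak gain. If this order is adopted, it should be fixed before any comparison of outcomes between the groups.
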